## Abstract

**Background:**

Depressive and anxiety disorders affect 20–30% of school-age youth, most of whom do not receive adequate services, contributing to poor developmental and academic outcomes. Evidence-based practices (EBPs) such as cognitive behavioral therapy (CBT) can improve outcomes, but numerous barriers limit access among affected youth. Many youth try to access mental health services in schools, but school professionals (SPs: counselors, psychologists, social workers) are rarely trained adequately in CBT methods. Further, SPs face organizational barriers to providing CBT, such as lack of administrative support. Three promising implementation strategies to address barriers to school-based CBT delivery include (1) Replicating Effective Programs (REP), which deploys customized CBT packaging, didactic training in CBT, and technical assistance; (2) coaching, which extends training via live supervision to improve SP competence in CBT delivery; and (3) facilitation, which employs an organizational expert who mentors SPs in strategic thinking to promote self-efficacy in garnering administrative support. REP is a relatively low-intensity/low-cost strategy, whereas coaching and facilitation require additional resources. However, not all schools will require all three strategies. The primary aim of this study is to compare the effectiveness of a school-level adaptive implementation intervention involving REP, coaching, and facilitation versus REP alone on the frequency of CBT delivered to students by SPs and student mental health outcomes. Secondary and exploratory aims examine cost-effectiveness, moderators, and mechanisms of implementation strategies.

**Methods:**

Using a clustered, sequential multiple-assignment, randomized trial (SMART) design, ≥ 200 SPs from 100 schools across Michigan will be randomized initially to receive REP vs. REP+coaching. After 8 weeks, schools that do not meet a pre-specified implementation benchmark are re-randomized to continue with the initial strategy or to augment with facilitation.

**Discussion:**

EBPs need to be implemented successfully and efficiently in settings where individuals are most likely to seek care in order to gain large-scale impact on public health. Adaptive implementation interventions hold the promise of providing cost-effective implementation support. This is the first study to test an adaptive implementation of CBT for school-age youth, at a statewide level, delivered by school staff, taking an EBP to large populations with limited mental health care access.

**Trial registration:**

NCT03541317—Registered on 29 May 2018 on ClinicalTrials.gov PRS

**Electronic supplementary material:**

The online version of this article (10.1186/s13012-018-0808-8) contains supplementary material, which is available to authorized users.

## Background

Depression and anxiety disorders are the most common mental health disorders among youth, affecting 20–30% of the population [1]. Evidence-based practices (EBPs), such as cognitive behavioral therapy (CBT), can improve outcomes among youth with these disorders [2–6]. However, less than 20% of youth with depression or anxiety have access to any EBPs, primarily because of limited availability of mental health providers, stigma, and lack of tools to implement effective treatments in the community [7–12]. Even when EBPs such as CBT are offered, fidelity to CBT treatment can be weak [6, 13–16] and most recipients do not receive an adequate therapeutic dose [17]. Without effective treatment, mental health disorders in youth can lead to poor developmental and academic outcomes, substance abuse, self-injury, adult psychopathology, and suicide [2, 18–21], ultimately resulting in immense social and economic costs [2, 18, 22].

EBPs need to be implemented successfully in settings where individuals are most likely to seek care if they are going to have a widespread and meaningful impact on public health. For many individuals with mental health disorders and for youth ages 14 to 21 in particular, non-clinical settings such as schools are attractive options for accessing EBPs [23–25]. Youth primarily spend their time in schools, which typically have school professionals (SPs) with training in social work, counseling, or psychology and who interface with students on a daily basis [22, 26, 27]. Students have reported more willingness to access mental health services at school than in other community settings [10, 11], and among youth who do receive any mental health care, 50–75% receive it exclusively in schools [12, 28]. However, the school professionals with whom they interact rarely have the training or support needed to provide EBPs [29].

Successful implementation of EBPs outside of traditional treatment settings requires scientific determination of optimal implementation strategies that maximize uptake and quality of care by addressing the organizational and community barriers to sustainability. Implementation strategies are highly specified, theory-based methods that target known barriers to improve uptake at provider and system levels [30]. However, implementation strategies designed to improve uptake of CBT among school professionals have not yet been empirically tested on a large scale. SPs do not routinely receive CBT training, and often report low confidence in their ability to deliver such treatments [31–33].

Promising theory-based implementation strategies for improving CBT uptake in schools are Replicating Effective Programs (REP), coaching, and facilitation. These strategies are potentially complementary to each other, but optimal combinations and sequences have not been tested empirically. REP, which is relatively low-burden to end-users [34, 35], focuses on customizing an intervention package to local needs and providing further support through large-group training and ongoing technical assistance [35]. REP has been shown to improve uptake of psychosocial EBPs in community organizations [35–39]; however, may not be sufficient for all providers requiring more supervision in delivering EBPs or for those who are experiencing organizational barriers to EBP adoption [38, 40]. Coaching provides ongoing live supervision of EBP delivery and has shown promise in facilitating CBT adoption in schools [33, 41, 42]. Facilitation includes consultation by an organizational expert in strategic thinking skills for providers to help them enhance organizational and leadership support for CBT implementation at their sites and has been shown to enhance uptake of psychosocial mental health interventions [34, 39].

Currently, there is no research to guide how best to combine REP, coaching, and facilitation for the purpose of CBT implementation in school settings. What is known is that schools, and the SPs that deliver mental health services at the schools, are heterogeneous in terms of barriers to CBT implementation [43]. Optimally efficient CBT uptake in schools may require a “stepped up” type of adaptive implementation intervention, whereby more intensive implementation strategies are only provided to schools that do not respond to a less intensive approach. In addressing barriers to uptake, augmentation of REP with coaching may be essential to overcome SP barriers, while facilitation may help with institutional barriers. Comparative research is needed to best combine these strategies to create and optimize an adaptive implementation intervention that maximizes uptake, cost-effectiveness, and sustainability of an established EBP (CBT), to ultimately improve student mental health.

This study seeks to build the best possible adaptive implementation intervention involving three theory-based implementation strategies—REP, coaching, and facilitation—using a clustered, sequential multiple assignment randomized trial (SMART) design. The study will foster development of an adaptive implementation intervention to improve frequency of CBT delivery to students by SPs, thereby reducing student mental health symptoms [44–49]. The study will take place in high schools across the State of Michigan.

## Methods/Design

### Aims and objectives

#### Primary study aim

The primary aim of this study is to compare the effectiveness of an adaptive implementation intervention on CBT delivery among schools versus REP alone (the control). The adaptive intervention provides schools with REP + coaching from the start and subsequently augments with facilitation for schools needing additional assistance. The primary outcome is the total number of CBT sessions delivered to students by SPs over an 18-month period. Number of CBT sessions is defined further below, and includes group and individual sessions delivered to students.

Specific CBT component delivery and whether delivery of individual or group sessions were brief (< 15 min) or full-length (≥ 15 min) will also be tracked and examined as secondary outcomes. As an exploratory outcome for this primary aim, we will also examine change in student mental health symptoms among students over the study period.

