### Study design

Figure 1 details the four phases of this study over an 18-month period; the four phases are 3, 2, 10, and 3 months in duration, respectively.

The run-in phase involves deployment of the REP implementation strategy (CBT manual package, training, and technical assistance) and identification of schools, SPs, and potential students in need of CBT by SPs.

For phase 1, eligible schools are randomized with equal probability to continued REP only versus REP combined with coaching (REP+coaching). At the end of phase 1, schools are assessed to determine whether they would potentially benefit from facilitation.

During phase 2, schools that could benefit from facilitation [39] (see Additional file 1: Appendix 1) will be re-randomized in phase 2 with equal probability to continue their implementation strategy from Phase 1 (i.e., REP or REP+coaching) or to have their current strategy augmented with facilitation (i.e., REP+facilitation or REP+coaching+facilitation, respectively). The active elements of the coaching and facilitation strategies will be paused during the summer months (June–August 2019) when schools are not in session.

For phase 3, all implementation strategies will be discontinued. Outcomes will be collected longitudinally throughout all phases, from SPs up to 18 months after the baseline assessment and from students up to 15 months after their baseline assessment.

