### Stratified randomizations

All randomization occurs at the school level. All study-eligible schools are randomized in phase 1 with equal probability to receive either REP or REP+coaching. In phase 2, schools with documented evidence of a need for additional implementation support based on predetermined criteria (see Additional file 1: Appendix 1) will be further randomized with equal probability to continue their phase 1 strategy (REP or REP+coaching) or to have their current strategy augmented with facilitation (REP+facilitation or REP+coaching+facilitation). To ensure balance across study arms, the first randomization will be stratified based on school size (> 500 or ≤ 500 students), location of school (rural or urban), percentage of students on free/reduced lunch program (≥ %50 or < 50%), and pre-randomization delivery of CBT (any sessions vs. none). The second randomization, among schools that might benefit from facilitation, will be stratified by size, location, and total number of CBT sessions provided in the 8 weeks post first randomization (top 50% vs. bottom 50% within REP or REP+coaching arm).

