#### Facilitation

Facilitation (Table 3) is based on the Integrated-Promoting Action on Research Implementation in Health Services Framework [73] and promotes provider self-efficacy [74] in mitigating organizational barriers to EBP adoption. Facilitation is delivered via regular phone contact for at least 10 weeks with the SPs by an expert in school and mental health care organization, implementation methods, and use of CBT and EBPs in schools. The facilitator will support SPs in strategic thinking and leadership skills to address organizational barriers covering the following:Initiation and benchmarking (week 1): facilitator contacts each SP to give background on CBT, review potential barriers and facilitators to CBT use (e.g., space to provide CBT, school administration support for the program), and set measurable goals for CBT uptake.Mentoring (weeks 2–9): facilitator and SP hold regular weekly calls to develop rapport; facilitator provides guidance to SP on overcoming specific barriers to CBT uptake by aligning SP strengths with SP available influence at the school and needs of local staff. If needed, facilitator refers SP to REP technical assistant (TA).Leveraging (weeks 2–10): facilitator continues calls with SP and reaches out to school administrators, identifies school/community priorities per administration input, and helps SP align CBT use/goals with these existing priorities. The facilitator helps SP summarize and describe added value of CBT to administrators and other school employees (e.g., consistency with other initiatives).Ongoing marketing (continuous): facilitator, leadership, and SP summarize progress and develop sustainability plans.

**Table 3 Tab3:** Data sources and measures*

Primary aim:	Measures	Measure frequency	Data sources
Primary outcome and endpoint	Total number of sessions of CBT delivered over the course of 18 months	Weekly, months 1–18 (no collection during summer months)	SP weekly survey
Secondary outcomes	Full sessions of CBT delivered; non-group CBT sessions delivered; brief sessions (< 15 min) of CBT delivered; CBT components delivered	Weekly, months 1–18 (no collection during summer months)	SP weekly survey
Exploratory outcomes	Student mental health outcomes (PHQ-9T; GAD-7)	Months 3, 6, 12, and18	Student survey administered by SP
	Student knowledge of CBT; reported CBT receipt	Months 3, 6, 12, and 18	Student survey administered by SP

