#### Aim 1 primary outcome (CBT delivery)

The *primary outcome* is the total number of CBT sessions delivered by each SP to students over the course of 18 months. To assess this outcome, SPs will complete a weekly survey where they report their weekly CBT delivery in group or individual sessions, as well as the compnents delivered.  Secondary outcomes will include different types of CBT delivery (individual vs. group; full sessions vs. brief) and delivery of specific CBT components. SPs will be compensated for weekly survey completion in the registry, and study staff will follow up with SPs who do not report CBT delivery for 4 weeks in order to remind them to complete data entry.

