### Sample size

The estimated sample size for this study is based on our primary aim: a comparison between the expected number of CBT sessions delivered by SPs between months 1 and 18 in schools receiving the adaptive implementation intervention (REP+ coaching + facilitation for schools that are eligible) versus the control (REP only). The sample size calculation for this comparison is a straightforward adjustment to the sample size calculation for a two-sample *t* test [88]. The first adjustment accounts for the clustering of SPs within schools (estimated interclass correlation = 0.03) to account for between-site variation induced by within-site correlation in SP CBT delivery outcomes. The second adjustment accounts for the rate of response following each phase 1 treatment by weighting schools differently to account for some schools being re-randomized and contributing to multiple experimental conditions. Using a two-sided test based on *k* = 100 schools (50 randomized to REP and 50 to REP+coaching in phase 1), on average ≥ 2 SPs per school (anticipated *N* ≥ 200 SPs), a type-1 error rate of 5%, ICC = 0.03, and assuming phase I response rates of 10% (REP only) or 50% (REP+coaching), we will have > 80% power to detect a moderate effect size of *D* = 0.53 between the two implementation interventions on number of CBT sessions delivered.

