### Trial status

The study has not started as of August 2018. In the run-in phase (October 2018–January 2019), all eligible SPs will receive Replicating Effective Programs (REP) components, including a 1-day didactic training in CBT in mid-January of 2019. The first randomization will occur in late January 2019.

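### The primary outcome counts CBT sessions from month 1, although months 1–3 precede the first randomization; starting the count at randomization is a free gain in precision

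*Protocol article*

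**What the plan says.** Under Primary study aim the article states: "The primary outcome is the total number of CBT sessions delivered to students by SPs over an 18-month period". The Measures section gives the same window per school professional (SP): "total number of CBT sessions delivered by each SP to students over the course of 18 months". Table 3 lists collection as "Weekly, months 1–18 (no collection during summer months", and the Sample size section bases its calculation on "the expected number of CBT sessions delivered by SPs between months 1 and 18". The Primary aim paragraph under Analyses also compares totals over 18 months.

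The Study design section fixes what those months contain: "the four phases are 3, 2, 10, and 3 months in duration, respectively". The first phase is the run-in, when REP is deployed to all schools. Schools are first randomized for phase 1. Trial status dates the run-in October 2018 to January 2019, places the one-day CBT training in mid-January, and adds: "The first randomization will occur in late January 2019".

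The first randomization is stratified on, among other factors, "pre-randomization delivery of CBT (any sessions vs. none". The plan therefore allows for some CBT being delivered before allocation. Nothing in the article starts the primary count at randomization or removes run-in sessions from it.

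**The concern.** An outcome meant to show the effect of allocation would normally begin at allocation. Here pre-randomization delivery serves as a baseline characteristic for stratification and is also summed into the outcome. Run-in sessions carry no information on the treatment contrast. Their between-SP variation, and any chance imbalance left after stratification, go into the primary comparison. The standardized effect shrinks, and any ratio of session counts moves toward 1. The design has little room for lost precision, because its stated power is only just above 80%.

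**Working it through.** **1. Where month 1 falls.** The phases sum to 3 + 2 + 10 + 3 = 18 months, so an 18-month window fits only if it opens with the run-in. Two other entries agree. Student surveys fall at months 3 to 18 in Table 3 and are described as 15 months of follow-up, which puts month 3 at the end of the run-in. Strategy costs are logged for months 1–15, which equals 3 + 2 + 10, the point at which the strategies stop. A clock starting at randomization fits none of these. The run-in is 3/18 = 16.7% of calendar months, or 3/15 = 20% of months with data collection once June–August is removed. These are shares of time, not of sessions.

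**2. The plan's own power.** Inputs from the Sample size section: 100 schools, 2 SPs per school, ICC 0.03, phase 1 response rates 10% and 50%, two-sided 5%, D = 0.53.
- Clustering factor: 1 + (2 − 1) × 0.03 = 1.03.
- SMART weighting factor, the mean of (2 − response rate) over arms: (1.90 + 1.50)/2 = 1.70.
- Schools needed for 80% power: 4 × (1.960 + 0.842)² / (2 × 0.53²) × 1.03 × 1.70 = 97.9, against 100 planned.
- Effective SPs per arm: 100 / (1.03 × 1.70) = 57.1. Noncentrality: 0.53 × √(57.1/2) = 2.83. Power: 80.8% (normal), or 80.1% with a t distribution on 98 df.

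The stated figure reproduces.

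**3. Effect of the run-in on the standardized effect.** Let s be the SD of the run-in count divided by the SD of the post-randomization count, and r their correlation. The expected absolute difference is the same with or without the run-in, but the SD of the total is larger by √(1 + s² + 2rs). Hence D(18-month) = D(post) / √(1 + s² + 2rs). The article gives neither s nor r, so the values below are assumptions, with r = 0.5.

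| s | SD inflation | Power for the 18-month total if 0.53 is the post-randomization effect | Power for the post-randomization count if 0.53 is the 18-month effect |
|---|---|---|---|
| 0.02 | 1.010 | 80.1% (D = 0.525) | 81.6% (D = 0.535) |
| 0.05 | 1.026 | 78.8% (D = 0.517) | 82.8% (D = 0.544) |
| 0.10 | 1.054 | 76.7% (D = 0.503) | 84.7% (D = 0.558) |

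The Sample size section attaches 0.53 to months 1–18, so the last column follows the plan's own terms.

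**4. Role of a baseline covariate.** In a linear model that includes the run-in count X, replacing the post-randomization count Y by Y + X raises the coefficient of X by exactly 1. The treatment estimate and its standard error do not change. Adjustment for X therefore removes the loss in step 3 whichever window is used. This identity does not carry over to a log-link model, where adding X to the outcome still pulls the rate ratio toward 1.

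**The case against.** The strongest reply has four parts.

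First, the article powers the same 18-month total that it defines, so 80.8% is the power of the endpoint as written and no shortfall has been shown. This stands. A reader might infer that power really falls to somewhere in the 60s or 70s. That inference moves D = 0.53 to a different endpoint and assumes substantial run-in delivery, and the article supports neither step.

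Second, run-in delivery is probably sparse. Training comes about two weeks before randomization, and eligible schools come from districts without earlier TRAILS CBT training. This also stands, and it makes the 20% share of collection time a poor guide to the share of sessions. Stratifying on any versus no sessions shows that delivery is not assumed to be zero. It does not show that much is expected.

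Third, that stratification limits chance imbalance between the arms. This is correct, but a two-level factor leaves the variation in counts inside the outcome.

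Fourth, the detailed analysis plan is in Additional file 3, which is not shown and may adjust for run-in delivery. In a linear model that would recover the precision, so the lack of a covariate in the article is not held against it. The outcome window, however, is fixed in the article itself.

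A reader might also take the window as a source of bias. It is not: allocation cannot change sessions that precede it, so the expected absolute difference and the type-1 error are unaffected.

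**Conclusion.** The mismatch is established from the article alone: the primary count opens three months before the first randomization. The consequence is confined to precision and to relative measures of effect, and its size cannot be determined from the article. On the plan's own reading of D = 0.53, counting from randomization would raise power from 80.8% to between about 81.6% and 84.7%, for run-in SD ratios of 0.02 to 0.10 and a correlation of 0.5. On the other reading, power for the present endpoint would lie between about 80.1% and 76.7% under the same assumptions. If run-in delivery is near zero, the two endpoints coincide. This is a worthwhile improvement, not a must-fix. Confidence is high on the window and low on the size of the gain.

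**What to change.** Define the primary outcome as the total number of CBT sessions delivered by each SP from the school's first randomization to month 18. Use the SP's run-in session count as a baseline covariate in the primary model, and keep the any-versus-none stratification factor. Align the wording under Primary study aim, in Table 3, in the Aim 1 primary outcome paragraph, in the Primary aim paragraph under Analyses, and in the Sample size section, which should also say which window D = 0.53 refers to. If the run-in is to remain in the count, state the reason.

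The cost is wording only. Weekly reports are already planned from month 1, so no new data are needed, and the article reports that the study had not started as of August 2018. If run-in delivery turns out to be negligible, nothing is lost.
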